## Introduction

Prostate cancer represents a large global public health problem, accounting for almost 1.4 million new cases yearly and being the second most common cancer diagnosis in men [1]. This large incidence, combined with its increasing survival rates, means that not only are growing numbers being diagnosed, but more men are now living with and beyond their disease [2]. Due to this, there is a growing realisation that living longer, and surviving disease, does not always equate to living well. With this in mind survivorship care in cancer has become an increasingly acknowledged topic with large initiatives globally, including the National Cancer Survivorship Initiative (NCSI) in the United Kingdom and similar programmes across the United States such as from the American Cancer Society (ACS) and the American Society of Clinical Oncology (ASCO) [3, 4].

When considering the impact of disease and treatment on prostate cancer patients long term wellbeing, the physical consequences, including urinary and sexual dysfunction, are well described [5]. However, it is only more recently that the mental wellbeing impact of disease is becoming recognised [6]. Mental health issues, particularly depressive and anxiety symptoms are prevalent in this group affecting an estimated 17% of individuals and translating into high suicidal ideation and mortality [7]. Additionally, other issues outside of pure mental health symptoms appear to be important in these men. This includes fear of cancer recurrence (FCR) or progression which has previously been labelled as one of the most common unmet cancer needs [8]. Along with Prostate-Specific Antigen (PSA) Anxiety, FCR is a prevalent issue in patients with prostate cancer [9]. Furthermore, issues surrounding masculinity, masculine-self-esteem and body image appear important in this population and represent constructs which assess the concept of self-worth representing the view of our body and mind and how it is perceived by others around us [10]. All these issues are of undeniable significance in prostate cancer care, not only in their prevalence, but also on the impact they have on treatment choices, functional outcomes and even mortality [11, 12].

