Importantly, the FCR7 scale items wording was adapted to ensure both recurrence and progression fear was evaluated to ensure ability of both baseline evaluation, and that of individuals not due to undergo curative treatments (e.g., active surveillance or hormone monotherapy). Similarly, the final item of the BIS (dissatisfaction with scar) was removed to ensure consistent evaluation between treatment groups. Internal consistency of these will be evaluated at conclusion through Cronbach’s alpha values to ensure they represent valid measures of these outcomes within the population.

Additional outcomes collected within questionnaires were validated measures of social, physical, and general health including:

The Expanded Prostate Cancer Index Composite-26 (EPIC-26)–Functional/Physical SymptomsFunctional Assessment of Cancer Therapy–General (FACT-G) Social Wellbeing Subscale–Social WellbeingShort Form– 12 (SF12)–Impact of disease on health

These outcomes will be utilised as both dependent and exposure variables depending on the subsequent analysis conducted.

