### Statistical analysis

Descriptive statistics will be calculated for the study population and individual study outcomes. Important definitions to be utilised throughout the data analysis are the threshold set for significant mental wellbeing symptoms in each of the measures collected. For depressive or anxiety symptoms a score of 10 or greater on the PHQ-9 or GAD 7 scales will be used for depression and anxiety respectively, representing moderate symptoms and has been demonstrated to correlate well to depressive or anxiety disorders diagnoses [23, 27]. For the FCR7 scale, a value of 17 or greater was selected, being representative of moderate fear of recurrence/progression as per the tool’s original development [24]. For the BIS, a cut of 10 or greater was selected as a previously demonstrated useful clinically relevant cut off point [28]. Finally, no clear-cut offs exist for the PC-QOL masculine self-esteem subset specifically. However, previously the tool authors have utilised scores of less than 60 to signify a low score for other subsets of the scale, and hence this was selected for this study [29].

Missing data during study follow-up through participant loss to follow up is expected, impacting subsequent analyses for primary and secondary outcomes. Where possible, multiple imputation will be considered for missing outcome data, with complete case analysis to be used for analyses where this is not possible.

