### Secondary outcomes

The following outcomes are not accounted for within the sample size calculations and are therefore considered exploratory. Each planned analysis will be divided per secondary aim of the study.

For exploration of prognostic factors of mental wellbeing outcomes, baseline patient, oncological and treatment factors previously described will be evaluated against the binary outcome of the development of significant individual mental wellbeing symptoms during study follow up. For this analysis an initial univariable, followed by a multivariable regression analysis of potentially significant individual prognostic factors is planned.The cumulative incidence of developing significant individual mental wellbeing outcomes during the 12-month study follow up will be calculated and presented as a percentage.To evaluate the trajectory of mental wellbeing symptoms over a 12-month period and effect of time on symptom scores, mental wellbeing outcome scores of whole cohort and individual treatment cohorts will be evaluated at each follow up time. Evaluation of these scores will be conducted using multilevel mixed-effects analyses to account for the effect of recruitment site clustering and expected loss to follow up during the study.The relationship between each individual mental wellbeing symptom and functional, social, and general health outcomes will be evaluated. Functional outcomes will include sexual, urinary and bowel symptoms from EPIC-26. Social wellbeing will include FACT-G subscale scores with general health defined using the SF-12 physical component score. All outcomes will be evaluated at 12-months. For this each mental wellbeing symptom will be continuously evaluated against these outcomes using univariable and subsequent multivariable linear regression, adjusted for known factors for functional and social outcomes.

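### Patient and oncological prognostic factors are tested only against a threshold-crossing event, losing roughly 40% to 55% of the information in the scores, and three of the five cut-offs are not established for the scale as used

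*Protocol article*

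**What the plan says.** Under Secondary outcomes, the first secondary aim is addressed by relating the baseline factors of Table 2 to an event, one per scale: they are evaluated "against the binary outcome of the development of significant individual mental wellbeing symptoms during study follow up". Univariable regression comes first, then a multivariable model of the factors that look promising. The same section says of all the secondary analyses: "The following outcomes are not accounted for within the sample size calculations and are therefore considered exploratory".

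The cut-offs are fixed under Statistical analysis:
- PHQ-9 and GAD-7: "a score of 10 or greater on the PHQ-9 or GAD 7 scales will be used for depression and anxiety respectively", with the stated support that this level correlates with diagnoses.
- FCR7: "For the FCR7 scale, a value of 17 or greater was selected", taken from the tool's development.
- BIS: 10 or more, from earlier published work.
- PC-QOL masculine self-esteem: below 60, with the admission that "no clear-cut offs exist for the PC-QOL masculine self-esteem subset specifically".

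Data collection and outcomes reports that two instruments were changed. For one, "the FCR7 scale items wording was adapted to ensure both recurrence and progression fear was evaluated"; for the BIS, the scar item was dropped. The check planned on the changed scales is Cronbach's alpha.

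Elsewhere the scores stay continuous: in the primary ANOVA at each visit, in the mixed models for trajectory, and in the regressions of functional and social outcomes at 12 months.

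**The concern.** The study aims to nominate prognostic factors for later research and models. A search of that kind depends on sensitivity, and a yes/no outcome treats a man just below the cut-off like one with no symptoms, and a man just above it like one with severe symptoms. With about 225 men left after the planned 25% dropout, the loss could decide whether a real factor is seen.

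The result also depends on where the line is drawn. For three scales the line has no documented basis for the version administered, and internal consistency, the only stated check, says nothing about whether a cut-off is in the right place.

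**Working it through.** **Plan's own figure.** The article gives no sample size or power for this analysis. Its only figure, 232, belongs to the primary ANOVA. It reproduces with two means 9.8 apart and two midway: f = (9.8/15.79) × √(1/8) = 0.219, giving 58 per group with power 0.803. It does not bear on this point.

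**Inputs from the article.** Target 300 and dropout 25% (Sample size), so 300 × 0.75 = 225. Follow-up visits at 3, 6, 9 and 12 months. Event rate: the Introduction describes depressive and anxiety symptoms as "affecting an estimated 17% of individuals". No rate is given for FCR7, BIS or masculine self-esteem.

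**Assumptions.** Normal scores, a small shift in the mean per factor, all visits complete, equal correlation ρ between any two visits, and no exclusion of men above the cut-off at baseline.

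**Step 1: one visit.** The efficiency of a split at event rate p, relative to the continuous score, is φ(z)² / [p(1−p)], where φ is the standard normal density and z cuts off a tail of p.

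| Event rate | Efficiency | Loss | 225 men act like |
|---|---|---|---|
| 5% | 0.224 | 78% | 50 |
| 10% | 0.342 | 66% | 77 |
| 17% | 0.454 | 55% | 102 |
| 30% | 0.576 | 42% | 130 |
| 50% | 0.637 | 36% | 143 |

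The loss exceeds one half only when the rate is below about 21% (or above 79%).

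In terms of power, take a two-level factor split 50/50 in 225 men. The standardised difference detectable with 80% power on the score is (1.96 + 0.84) × √(4/225) = 0.374. On the binary outcome the same difference has about 37% power at a 10% rate, 46% at 17% and 56% at 30%.

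**Step 2: the planned event.** The event is crossing at any follow-up visit, so more men have it than at one visit. A simulation of 1,000,000 men compared it with the mean of the four scores. Binary information is (dP/dshift)² / [P(1−P)], where P is the proportion ever crossing. The mean of four scores carries 1 / [ρ + (1−ρ)/4]. For example, at 17% per visit and ρ = 0.7, binary information is 0.706 and continuous information is 1/0.775 = 1.290, so the efficiency is 0.706/1.290 = 0.547.

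| Rate per visit | Ever crossing (ρ = 0.85 to 0.5) | Loss over ρ = 0.5, 0.7, 0.85 |
|---|---|---|
| 10% | 18% to 26% | 54% to 56% |
| 17% | 28% to 39% | 45% to 49% |
| 30% | 45% to 59% | 39% to 47% |

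The range is therefore roughly 40% to 55%.

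**Step 3: cut-offs beside the instruments.**
- Masculine self-esteem: by the article's own account there is no specific cut-off, and 60 comes from other subsets.
- BIS: one item fewer, same cut-off. If items score zero or more and the published cut-off was for the full scale, the total can only fall, so 10 is stricter than the published threshold.
- FCR7: wording changed and no item reported removed. The published 17 is unverified for this version, not shown to be wrong.

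**The case against.** The best defence is that caseness is a legitimate target. The article wants to identify men who need extra monitoring or support, the same thresholds serve the separate incidence aim, and the analysis is declared exploratory and unpowered. A change in mean score is a different question, and an extra continuous model or a cut-off sensitivity analysis could sit in a fuller plan. The clinical interest in caseness stands and is a reason to keep the binary analysis. It is no reason to make it the sole stated one, and the exploratory label does not help, because a search for candidate factors is where lost sensitivity costs most.

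It also stands that continuous scores do not undo the changes to the BIS and FCR7. The altered totals would still be the outcome; only the dependence on a cut-off goes away.

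A reader might infer three stronger points that the article does not support:
- That no prognostic analysis uses the scores. Treatment is compared on continuous scores in the primary ANOVA, and time since diagnosis in the mixed models. The gap concerns patient and oncological factors.
- That more than half the information is lost. This holds for a single-visit split at 17%. For the planned event at 17% per visit the loss is 45% to 49%, and it passes one half only at lower rates.
- That there are about two events per factor (225 × 0.17 = 38 events over some 19 factors in Table 2). This needs all factors in one model and 17% as the rate of ever crossing. The plan screens factors first, and 28% to 39% ever crossing gives 63 to 88 events if men above threshold at baseline are kept.

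**Conclusion.** The point holds for patient and oncological factors. The stated analysis discards a substantial part of the information already collected: roughly 40% to 55% for the planned event under the scenarios above. These figures rest on normal scores, small shifts and assumed correlations and event rates, and skewed scores would change the exact percentages. If men above the cut-off at baseline are excluded, which the wording leaves open, the event rate falls and the loss moves towards the upper end.

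The cut-off criticism is firm for masculine self-esteem, firm for the BIS given non-negative item scores and a full-scale source cut-off, and weaker for FCR7. The PHQ-9 and GAD-7 cut-offs are not in question. A reader might infer that three scales simply have no cut-off; the article shows that only for masculine self-esteem.

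This is a worthwhile and cheap gain in precision for an exploratory aim. It does not affect the primary analysis.

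**What to change.** State as the main prognostic analysis, for each scale, a regression or mixed model of the continuous follow-up score on the listed factors, adjusted for the baseline score. The mixed model already planned for trajectories can carry this.

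Keep the threshold event as a supportive analysis that clinicians can read directly, chiefly for PHQ-9 and GAD-7. If it is also reported for BIS, FCR7 and masculine self-esteem, repeat it over a range of cut-offs and say that those used are not established for these versions.

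No new data are needed. The cost is a change of wording and modest extra modelling. The downside is that coefficients in scale points are less directly clinical than odds of caseness, which is why the binary version stays.

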**Fig 2 pone.0284727.g002:**
[figure not shown]
Study timeline.

**Table 2 pone.0284727.t002:** Exposure variables collected for subsequent prognostic evaluation during the study.

**Patient Factors**	Age at diagnosis, ethnicity, relationship/co-occupancy status, employment status, smoking status, alcohol intake, index of multiple deprivation, medical co-morbidities, current or previous mental health history, family history of mental health conditions and family history of prostate cancer
**Oncological Factors**	Gleason grade and ISUP classification, number of positive biopsy cores, risk stratification, PSA at diagnosis, TNM Score and stage classification.
**Treatment Factors**	Final treatment received, presence of positive surgical margins

Primary study outcomes collected within questionnaires included validated psychometric measures for mental wellbeing post prostate cancer diagnosis. Important mental wellbeing outcomes were defined through multiple extensive and systematic searches of the existing literature due to variable current definitions [7, 9, 10]. This selected five mental wellbeing constructs of interest which will be included within the overall primary outcome of ‘mental wellbeing’:

Depressive SymptomsAnxiety SymptomsFear of Cancer Recurrence/ProgressionBody Image PerceptionMasculine Self-Esteem

Selection of subsequent validated psychometric measures for these outcomes was based on the most utilised tools, or those with the best psychometric properties within a prostate cancer population. These were defined by previous reviews or through a dedicated review for body image and masculinity outcomes [7, 9, 21]. Final psychometric scales selected were:

Patient Health Questionnaire (PHQ)-9—Depression symptoms [22]Generalised Anxiety Disorder (GAD)-7 –Anxiety symptoms [23]Fear of Recurrence Scale 7 (FCR7)—Fear of cancer recurrence/progression [24]Body Image Scale (BIS)–Body image perception [25]Prostate Cancer-Quality of Life (PC-QOL) Masculine Self-Esteem Subset–Masculinity [26]

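### Prognostic factors are chosen by univariable screening of 18 to 20 overlapping candidates with few events each, and surgical margins are treated as a baseline factor

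*Protocol article*

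**What the plan says.** The first item under Secondary outcomes states that "baseline patient, oncological and treatment factors previously described will be evaluated against the binary outcome" of developing significant symptoms on each construct during follow-up. The method is: "For this analysis an initial univariable, followed by a multivariable regression analysis of potentially significant individual prognostic factors is planned". No screening threshold or limit on model size is given.

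The factors previously described are those in Table 2:

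- Patient: "Age at diagnosis, ethnicity, relationship/co-occupancy status, employment status, smoking status, alcohol intake, index of multiple deprivation, medical co-morbidities", then "current or previous mental health history, family history of mental health conditions and family history of prostate cancer".
- Oncological: "Gleason grade and ISUP classification, number of positive biopsy cores, risk stratification, PSA at diagnosis, TNM Score and stage classification".
- Treatment: "Final treatment received, presence of positive surgical margins".

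The five constructs are depression, anxiety, fear of recurrence or progression, body image and masculine self-esteem. Secondary outcomes calls these analyses exploratory and outside the sample size. The Discussion says that the findings should help choose candidate predictors for later prognostic models, and may help identify men at higher risk.

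**The concern.** Two things look wrong.

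1. **Selection.** Choosing the multivariable model by univariable results lets chance decide which factors appear. With many candidates and few events, some null factors get through. True factors that get through do so partly because their estimates happened to be large. Others are lost, either to low power or because confounding masks them in an unadjusted test. Several oncological entries (grade, PSA, TNM or stage, risk group) describe overlapping aspects of disease severity, so which of them survives is partly arbitrary. Study aims already hypothesises age, mental health history, comorbidities and stage, yet nothing stated protects these from being screened out.

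2. **Margins.** The Secondary outcomes wording puts treatment factors, and so "presence of positive surgical margins", among baseline factors. Margins are known only after surgery and have no meaning for men on surveillance, radiotherapy or hormone monotherapy.

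At stake is the list of factors passed on to later prognostic research. The primary ANOVA comparisons are not affected.

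**Working it through.** **Sample size available.** The only sample-size figure in the article is for the primary ANOVA. With a difference of 9.8 and SD of 15.79, d = 9.8/15.79 = 0.621. With two extreme groups and two at the midpoint, f = 0.621 × √(1/8) = 0.219. At alpha 0.05 and power 0.80 this gives 58 per group, 232 in all (power 0.803), which matches the article. There is no corresponding figure for the prognostic analysis. I therefore use the target of 300, and 300 × 0.75 = 225 after the stated 25% dropout.

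**Candidates.** 11 patient + 5 oncological + 2 treatment = 18. Splitting Gleason/ISUP and TNM/stage gives 20.

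**Events per candidate = rate × N / candidates.** The only rate in the article is in the Introduction: depressive and anxiety symptoms "affecting an estimated 17% of individuals". It is a prevalence for those symptoms, not a 12-month incidence, and nothing comparable is given for the other three constructs. It is used here as an assumption, with a range around it.

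| Assumed rate | Events, N = 225 | Events, N = 300 | Events per candidate (225/20 to 300/18) |
|---|---|---|---|
| 10% | 22.5 | 30 | 1.1 to 1.7 |
| 17% | 38.3 | 51 | 1.9 to 2.8 |
| 25% | 56.3 | 75 | 2.8 to 4.2 |
| 40% | 90 | 120 | 4.5 to 6.7 |

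Coding the categorical factors lowers these further. With an assumed 30 to 40 parameters and a 17% rate, the range is 38.3/40 = 1.0 to 51/30 = 1.7.

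**False positives if no candidate matters.** With independent tests at 0.05, the expected number per outcome is 18 × 0.05 = 0.9 to 20 × 0.05 = 1.0, or 4.5 to 5 over five outcomes. The chance of at least one is 1 − 0.95^18 = 0.60 to 1 − 0.95^20 = 0.64. A simulation of the two-step procedure used 20 noise candidates, N = 225 or 300, rates of 17%, 30% and 40%, and screens at p < 0.05 and p < 0.20 (500 runs each). At least one noise factor ended significant in the multivariable model in 58% to 68% of analyses in every setting. The result therefore depends little on the assumed rate or the unstated threshold.

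**Share of false factors when some are real.** This simulation used 18 independent candidates, a 17% rate, the same two screens and 150 runs per setting.

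- 3 to 6 true factors at odds ratios of 1.3 to 1.5 per SD: 16% to 37% of the finally significant factors were false.
- 2 true factors at 1.3: 47% to 63% were false.

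**Exaggeration and loss.** Take a true log-odds of 0.30 per SD and a screen at p < 0.05. At N = 225 and 17%, the SE is about 1/√(225 × 0.17 × 0.83) = 0.177, so z = 0.30/0.177 = 1.69 and the chance of passing is about P(Z > 1.96 − 1.69) = 0.39. Simulation (3000 runs) gave 38%, with a mean selected estimate of 0.50. At N = 300 and 40%, the factor was still missed 30% of the time and averaged 0.36 when selected.

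**Margins.** Population excludes men who are already post-surgery, so no participant has a margin result at baseline. The target is 75 men per cohort, and 75 × 0.75 = 56 after dropout. At the assumed 17% that is 0.17 × 75 = 12.8 or 0.17 × 56.25 = 9.6 events. Under Statistical analysis, multiple imputation is considered only for missing outcomes, with complete-case analysis otherwise. A whole-cohort complete-case model containing margins would therefore retain the prostatectomy cohort alone. Treatment would be constant in it and could not be estimated.

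**The case against.** The strongest reply is that the article already limits what it claims. It calls the analysis exploratory in several places, says it is outside the sample size, and says that the factors need evaluation in further studies. It gives no p-value for the screen, and a threshold, forced variables or a coding rule for margins may sit in a fuller plan. This stands in part: it lowers the severity and rules out several stronger readings.

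- A reader might infer that the nominated factors will be mostly noise. The article does not support that. In the simulations the false share exceeded half only with few, weak true factors or none.
- A reader might take 38 to 51 events per outcome as the plan's figure. It is not. It applies a depression and anxiety prevalence to five outcomes. Repeated assessment could raise the count, and excluding men already above threshold at baseline could lower it.
- A reader might say that three cohorts will be lost. That follows only if margins enter a whole-cohort complete-case model. It does not follow with a not-applicable level or a prostatectomy-only analysis, and the article does not say which is intended.
- A reader might say that the plan promises independent prognostic factors. It does not; that word is used only for regressors.

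What the reply does not answer is the procedure itself. The univariable-then-multivariable sequence is stated, not left open. An exploratory label disclaims power but does not remove selection bias, and choosing candidates is the use to which the Discussion puts the results.

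**Conclusion.** The point holds in limited form. The stated procedure screens 18 to 20 overlapping candidates for each of five outcomes with few events per candidate: about 2 to 3 if 17% is assumed, and below 7 even at an assumed 40%. It can be expected to yield some false factors, to overstate the effects it selects and sometimes to drop hypothesised ones. How large the false share is depends on how many factors are truly prognostic, which the article cannot tell us. The simulations also assume independent, normally distributed candidates, which the Table 2 entries are not.

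The margins problem needs no assumed rate: a post-surgical finding defined in one cohort of four is grouped with baseline factors for the whole study. Its consequence, a model reduced to about 75 men (about 56 after dropout) with no treatment contrast, is conditional on how margins are entered.

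This is worth correcting before analysis. It does not bear on the primary comparison.

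**What to change.** Replace the univariable screen with one pre-specified model per outcome. It should contain the factors hypothesised in Study aims (age, mental health history, comorbidity, stage), the management group, and the baseline score on the same scale. That score is already collected but is not in Table 2. Use penalised estimation, such as Firth or ridge, where events are few. Report each remaining candidate one at a time, adjusted for that core and labelled exploratory, whatever its p-value.

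Take margins out of the baseline list. Analyse them only within the prostatectomy cohort, using visits after surgery, and state the number of men and events.

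The cost is analysis wording and standard software, with no new data. The downside is that fewer factors receive a mutually adjusted estimate.
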